## 8. TRIAL PROCEDURES

### 8.1 Recruitment

Participants will be recruited at five sites:

1. University of Worcester
2. University of Brighton
3. Oxford-Brookes University
4. Bournemouth University
5. University of Hertfordshire

The research assistant will present the study to the Year 1, 2, and 3 cohorts at collaborating universities. Interested students will be asked to provide their email address so that a link may be emailed to them which includes the Participant Information Sheet (PIS). The PIS contains the contact details of the researchers so potential recruits may contact them with any queries. Interested participants will be invited to ask any questions.

If participants decide that they would like to take part, they will have the option of giving consent, online, or the option to ask further questions. If they endorse the latter, the researcher will email the participant to schedule a time to speak on the telephone to answer their questions.

Once participants' questions have been answered and if they wish to give consent or if they have no questions and wish to give their consent, they will be required to confirm that they understand the various points of the study and electronically signing their name. Once they have given consent online, they will be asked to complete the two screening questionnaires. It will be made clear that participation is entirely voluntary and that volunteers may withdraw from the study at any point without incurring any negative consequences.

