#### 8.4 Randomisation

Random allocation to the three trial conditions (iCT, Mind-Online, standard practice) will be at a 1:1:1 ratio, stratified by site and initial eligibility (above or below cut-off on PHQ-9 and PCL-5 at screening) by the Oxford Clinical Trials Research Unit (OCTRU).

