## **Randomisation and Blinding**

Participants are randomised on a 1:1:1 ratio as per a computer-generated randomisation schedule by OCTRU (Oxford Clinical Trials Research Unit) stratified by site, gender and baseline PHQ-9 score ( $\geq 9$  vs.  $< 9$ ) and PCL-5 score ( $\geq 33$  vs.  $< 33$ ). The researchers inform participants of the intervention they are to receive after participants have completed baseline assessments. Outcome assessment is single blind. Online questionnaires throughout the intervention and follow-up time points are completed without any involvement of the researchers. The clinical interview is done by an independent assessor, who is blind to treatment allocation. All personnel involved in the blood and saliva samples are blinded to intervention allocation. Due to the nature of the interventions, participants cannot be completely blinded to allocation.

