## **Statistical Analysis Outline**

Linear and logistic mixed effects modelling are used to test the primary and secondary trial objectives (with the exclusion of the health economic analyses, which will be conducted by [name] and therefore not part of this analysis plan, as well as the hormone and immune function analyses which will be conducted by Professors [name] and [name]), which is the standard technique for analysing clinical trials.

For the primary and secondary trial objectives, 1-year follow-up is the short-term primary outcome time point (except for immune and hormone function for which the time-point is post-intervention), PTSD and MDD diagnoses are the primary outcome measures. Once completed, the 2-year PTSD and MDD diagnoses at 2-year follow-up are the long-term and main primary outcome time points.

Both repeated assessments and intervention arm are specified as categorical variables for reasons of flexibility in the modelling approach. Repeated assessments, intervention arm, their interaction effects, and baseline scores and covariates are estimated as fixed effects and random effects are estimated for time (level 1) nested within the participants (level 2). An unstructured variance-covariance matrix is used to model the error correlation structure within the participants.

Global comparisons for the main effect of intervention group and the interaction effects between time and intervention group are tested for primary and secondary trial objectives and further group comparisons are carried out if the global comparisons are significant. The hierarchy of the group comparisons reads as follows: 1) iCT-R versus Mind-Online, 2) iCT-R versus Standard Practice, and 3) Mind-Online versus Standard Practice. Site is introduced as a random effect in the analyses of the primary trial objectives. If non-significant, site will not be carried forward into further trial analyses.

Maximum Likelihood estimation is used. Assumptions for mixed effects modelling are tested and normality of residuals are confirmed for the outcome measures. If assumptions are violated, resampling approaches will be used.

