## **Analysis Methods**

Analyses of the primary trial objectives:

To analyse any differences between the intervention arms in terms of effectiveness with regards to rates of PTSD and MDD diagnoses (SCID-5) at 1-year follow-up (short-term primary outcome time point) and at 2-years follow-up (long-term primary outcome time point once completed), intervention condition and the interaction between intervention time and

intervention group on rates of PTSD and MDD diagnoses, logistic mixed effects models with PTSD and MDD diagnoses as outcomes (short-term outcome 1-year follow-up data, long-term outcome 2-years follow-up once completed) are specified and analysed.

To analyse any differences between the intervention arms in terms of effectiveness with regards to PTSD symptom severity (PCL-5) or MDD symptom severity (PHQ-9) at 1-year follow-up (short-term primary outcome time point) and at 2-years follow-up (long-term primary outcome time point once completed), intervention condition (categorical; iCT-R versus Mind-Online versus Standard practice; level 2) and the interaction between intervention time (categorical; post-intervention, 6-months follow-up; 1-year-follow-up, 2-year follow-up, once completed; level 1) and intervention group on PTSD or MDD symptom severity, linear mixed effects models with either PTSD or MDD symptom severity as outcomes are specified and analysed.

Both repeated assessments and intervention arm are specified as categorical variables for reasons of flexibility in the modelling approach. Repeated assessments/ time, intervention arm, both their interaction effects, and baseline scores and covariates are estimated as fixed effects and random effects are estimated for time (level 1) nested within the participants (level 2). An unstructured variance-covariance matrix is used to model the error correlation structure within the participants. Estimation method is Maximum Likelihood. Normality of the residuals for the outcomes is confirmed visually.

Randomisation has been done by stratification by site, gender, and baseline PTSD symptom severity and MDD symptom severity. Therefore, baseline PTSD symptom severity and MDD symptom severity and randomisation factors are added as covariates in these models. Site is added as random factor in those models. If non-significant, they will not be carried forward into further analyses.

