Linear mixed effects models are specified for these continuous outcome measures. Intervention condition (categorical; iCT-R versus Mind-Online versus Standard Practice; level 2) and the interaction between intervention time (categorical; post-intervention, 1-year-follow-up, 2-years-follow-up once completed; level 1) are specified as fixed effects predictors in the models.

Baseline values for the respective secondary outcome are added as covariate in these models together with PTSD and MDD symptom severity at baseline, and randomisation factors.

Adjusted/ estimated mean differences and Cohen's d's with standard deviation at baseline in the denominator are reported in tables for continuous outcomes for the intervention effects from results of linear mixed effects models.

The health economic analyses will be conducted and reported by [name] and and hormone and immune function are tested by collaborators and are therefore not part of this statistical analysis plan. A plan for the health economic and hormone and immune function analyses will be agreed.

Analyses of the tertiary trial objectives:

In order to investigate whether risk factors and predictors at baseline, such as level of social support, trauma exposure, demographic data, past and current comorbidities, neuroticism as a personality factor, level of concrete thinking, and frequency/ duration/ distress with regards to intrusive memories, influence any iCT-R intervention effects on PTSD or MDD diagnoses, psychological distress, and well-being at 1-year follow-up, a mixed effects model for each of the outcomes, PTSD and MDD diagnoses, psychological distress, and well-being, is specified with baseline scores of PTSD or MDD symptom severity or psychological distress or well-being as covariate. The main effects of the respective baseline predictors (time-invariant covariates) and the two-way interactions between each of those baseline predictors and time (categorical: post-intervention, 1-year follow-up; level 1) will be analysed.

Again, Maximum Likelihood is used if the assumption of normality of the residuals of the outcomes is fulfilled. An unstructured variance-covariance structure matrix is used, all significance tests are carried out on a  $p < .05$  level, two-sided, and confidence intervals are reported at the 95% level.

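### The SAP drops site, a five-level randomisation stratifier, from later models on an unnamed, low-powered significance test; the numerical effect is small, but the rule is data-driven, ambiguous and inconsistent with the rest of the plan

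*Combined protocol and SAP*

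**What the plan says.** **Design.** Protocol 8.1: "Participants will be recruited at five sites". Protocol 8.4 has allocation "stratified by site and initial eligibility (above or below cut-off on PHQ-9 and PCL-5 at screening". SAP Randomisation and Blinding has it "stratified by site, gender and baseline PHQ-9 score", plus a PCL-5 cut-off. Gender is therefore a stratifier in the SAP and is not named in the protocol.

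**Primary-objective models.** SAP Statistical Analysis Outline: "Site is introduced as a random effect in the analyses of the primary trial objectives". It continues: "If non-significant, site will not be carried forward into further trial analyses". SAP Analysis Methods says that "baseline PTSD symptom severity and MDD symptom severity and randomisation factors are added as covariates in these models", and then: "Site is added as random factor in those models. If non-significant, they will not be carried forward into further analyses".

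**Secondary-outcome models.** The same SAP section adds the baseline value of the outcome "together with PTSD and MDD symptom severity at baseline, and randomisation factors", with no significance condition.

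**Protocol analysis.** Section 11.1.1 treats site as the third level of the hierarchical model for continuous measures, again with no condition.

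**Timing.** SAP Timing of Final Analysis brings the main analysis forward to 1 year and adds the 2-year data to the 1-year outcome models later. SAP Statistical Analysis Outline calls 2 years the long-term and main primary time point.

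**The concern.** A factor that was balanced by design belongs in the analysis whatever its p-value. Making it conditional raises four problems.

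1. The test has little power with five sites, so a non-significant result is weak evidence that site can be ignored.
2. The rule cannot be carried out as written. No test or threshold for a variance component is given. Four outcomes serve the primary objective (PTSD diagnosis, MDD diagnosis, PCL-5, PHQ-9), and nothing says which one decides if they disagree. The choice would be made after seeing data.
3. Its scope is unclear. The Outline limits it to site. The plural in Analysis Methods follows a list of baseline severity, randomisation factors and site, and could cover any of them. The secondary-outcome text then requires the randomisation factors without condition.
4. The SAP does not say whether the 2-year models count as further analyses. If they do, the model at the main primary time point would depend on 1-year results already seen by arm.

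At stake are pre-specification and consistency of the estimand across models, more than the size of any p-value.

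**Working it through.** **Plan's own figure.** Protocol 11.2 uses 25% against 12.5%, 80% power and alpha 0.05. A two-sided comparison of two proportions with pooled variance and no continuity correction gives 151.9, so 152 per arm and 304 for two arms. The odds ratio is (0.125/0.875)/(0.25/0.75) = 0.429. Three arms need 456, and 456/0.8 = 570. The plan's figures are reproduced and nothing here changes them. They supply the analysed number: 456/5, or about 91 per site if sites are equal.

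**Assumption.** The documents give no site ICC. I use 0.01 to 0.05, and go to 0.10 where shown.

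**How often a real site effect is dropped.** For an F-test of five sites of 91, P(drop) = P(F(4,450) < 2.39/[1 + 91 × ICC/(1 − ICC)]).
- ICC 0.01: 2.39/1.919 = 1.25, drop 71%.
- ICC 0.02: 2.39/2.857 = 0.84, drop 50%.
- ICC 0.05: 2.39/5.789 = 0.41, drop 20%.
- ICC 0.10: 2.39/11.11 = 0.215, drop 7%.

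The SAP estimates by maximum likelihood, so a likelihood-ratio test of the site variance is closer to its text. In 20,000 simulated trials per setting (continuous outcome, one time point, five sites, 30 per arm per site), that test drops site in 88%, 71% and 35% of trials at ICC 0.01, 0.02 and 0.05. With the boundary correction the figures are 83%, 63% and 29%.

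**Cost of always omitting site (linear model).** Balance within site removes between-site variance from the treatment contrast, but the model without site leaves it in the residual. The standard error is too large by r = 1/√(1 − ICC). The true error is 2Φ(−1.960r), and power is Φ(2.802 − 1.960r), where 2.802 = 1.960 + 0.842.

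| Assumed ICC | r | True two-sided error | Power |
|---|---|---|---|
| 0.01 | 1.005 | 4.9% | 79.7% |
| 0.02 | 1.010 | 4.8% | 79.4% |
| 0.05 | 1.026 | 4.4% | 78.5% |

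**Cost of the rule itself.** In the same simulations (ICC 0 to 0.05), keep-or-drop gives type I error 0.047 to 0.051 and power 0.796 to 0.801. Always keeping site gives 0.048 to 0.051 and 0.796 to 0.802. In the trials where site is dropped, the mean excess in standard error is at most about 0.5%.

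**Logistic models.** 2,000 simulated trials per setting, site SD 0.2, 0.4 and 0.6 on the logit scale, true odds ratio 0.429. Site is dropped in about 79%, 40% and 17% of trials. The absolute log odds ratio averages 0.868, 0.863 and 0.867 with site kept and 0.857, 0.839 and 0.825 with it omitted. As odds ratios, that is 0.420, 0.422 and 0.420 against 0.424, 0.432 and 0.438. Type I error under the rule is 0.048, 0.048 and 0.052. Dropping site moves the odds ratio from conditional on site towards marginal over sites.

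**The case against.** The strongest reply is that the rule is nearly harmless. It tends to drop site when site hardly matters, and to keep it when it does. That stands. A reader might pair the high drop rates with a large loss of power, but the two do not occur together: the drop rates of 71% and 50% go with power of 79.7% and 79.4%, and at ICC 0.10 the F-test drops site in only 7% of trials.

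Other stronger readings are also not supported:
- *Standard errors that produce false positives.* Omitting a balanced stratifier makes them slightly too large, so the error is conservative.
- *Site is lost from the primary analysis.* The models in which site is tested keep it. Only the 2-year models are in doubt.
- *Each outcome selects its own covariates.* The Outline takes the decision in the primary-objective models and carries it forward; it does not re-test site for each outcome.
- *A random effect with five levels is an error.* It still models site, and the protocol already had site as a level. Fixed or random is a preference.
- *One document must describe the wrong adjustment for gender.* Protocol 8.4 describes allocation only, and adjusting for gender is valid even if it was not a stratifier. This is a documentation mismatch.
- *All stratifiers will be dropped.* The Outline names site alone, and the secondary-outcome text keeps the randomisation factors. The plural permits the wider reading but does not establish it.

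None of this justifies the rule. It gains at most a few degrees of freedom, cannot be carried out as written, and conflicts with other text in the plan.

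**Conclusion.** The point holds as one of specification. Dropping a stratifier on a test with little power at five sites, with no named test, no rule for disagreement among outcomes and an unclear scope, leaves later models to be settled by the data. It contradicts the SAP's own secondary-outcome text and departs from protocol 11.1.1. Its possible reach into the main 2-year models is the most important gap.

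The numerical effect for site alone is small and conservative: true error of about 4.9% to 4.4% and power of 79.7% to 78.5% if site were always omitted at ICC 0.01 to 0.05, near-nominal error and power under the rule, and a slight attenuation of logistic odds ratios. These figures rest on assumed site variation and equal site sizes, with a single time point in the continuous simulations. The change should be made because it is nearly free and removes a post-hoc choice. The documents do not show that the rule would bias the trial's result.

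**What to change.** 1. Delete the conditional sentence on site in SAP Statistical Analysis Outline and its counterpart in Analysis Methods.
2. State that site (fixed or random, chosen now) and every stratification factor actually used stay in all primary and secondary models whatever their p-values, and say explicitly that this covers the 2-year models.
3. Check protocol 8.4 against SAP Randomisation and Blinding and Analysis Methods on gender, using the randomisation schedule held by the trials unit, and correct whichever text is wrong.

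The cost is a few lines of SAP wording and a few degrees of freedom (four for site if fixed). The sample size of 570 is unaffected.

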## **STATISTICAL PRINCIPLES**

### **Statistical Significance and Multiple Testing**

In the case of different scaling, continuous variables are standardized for the analysis. Global comparisons are tested and if significant, group comparisons are then carried out.

[name], [name], [name], [name], [name], [name], [name], [name], [name], [name], [name], & [name] Cognitive resilience training to prevent PTSD and MDD in paramedics: A randomised controlled trial.

If not specified otherwise, one or the other, main effects of intervention group or interaction effects between intervention group and time in favour of iCT-R, indicate intervention superiority.

All analyses will be carried out with a significance level of  $p < .05$ , two-sided.

No adjustments for multiple testing are made, as the primary trial objective is to evaluate any superiority in efficacy of the new resilience intervention compared to the existing online intervention (group comparison between these two groups of highest priority and directive hypothesis).

Confidence intervals are reported at the 95% level, two-sided.

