## **Objectives**

The primary trial objective is to evaluate whether the newly developed iCT-R intervention is more effective than the existing Mind-Online intervention at 1-year and at 2-years follow-up with regards to PTSD and MDD diagnoses.

Secondary trial objectives are to evaluate the efficacy of iCT-R compared to Mind-Online at 1-year and at 2-year follow-up with regards to secondary outcomes, such as resilience and well-being measures, as well as general health measures, and in terms of health economic costs. Furthermore, the effects of iCT-R versus Mind-Online on immune and hormone function will be compared at post-intervention.

Tertiary trial objectives are to investigate whether risk factors and predictors at baseline, such as level of social support, trauma exposure, demographic data, neuroticism as a personality factor, level of concrete thinking, frequency, duration, and distress with regards to intrusive memories influence any effects of iCT-R on PTSD and MDD diagnoses, psychological distress, and well-being at 1-year follow-up.

Further tertiary objectives are to investigate whether changes from baseline to post-intervention in resilience factors, such as rumination, responses to intrusive memories, level of concrete thinking, and resilience appraisals, predict PTSD and MDD diagnoses at 1-year follow-up in the iCT-R intervention group.

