Measures to test the tertiary trial objective are risk factors and predictors at baseline, such as level of social support (adapted from a brief measure of social support), trauma exposure (trauma screener), demographic data (general information questionnaire), neuroticism as a personality factor (subscale neuroticism from the Eysenck Personality Questionnaire), level of concrete thinking (CAT), and frequency, duration, and distress with regards to intrusive memories (Intrusions Questionnaire).

More information on the outcome measures can be found in the published trial protocol ([name] et al., 2018).

Time points:

Data are collected at pre-intervention, post-intervention, at 6-months follow-up, at 1-year follow-up and at 2-years follow-up. PTSD and MDD diagnoses are assessed pre-intervention, post-intervention, at 1-year and at 2-years follow-up, PTSD and MDD symptom severity are assessed at all measurement points. Secondary outcome measures are assessed at pre-intervention, post-intervention, and at 1-year and at 2-years follow-up. All measures for the tertiary trial objective are assessed at pre-intervention, at 1-year and at 2-years follow-up. All tertiary measures (except for demographics) are assessed at post-intervention, and trauma exposure, concrete thinking and intrusion measures are collected at 6-months follow-up, as well.

For the early analysis of the trial results, 1-year follow-up is the short-term primary outcome time point. Once the trial has been completed, the primary outcome time point is 2-years follow-up as described in the published trial protocol.

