In case of a significant main effect of intervention group or interaction effect between intervention group and time with regards to the primary outcome measure (PTSD and MDD diagnoses) and secondary outcome measures for the primary trial objective (PTSD and MDD symptom severity), intervention group comparisons are carried out using pairwise contrasts. iCT-R (coded as '1') is tested against Mind-Online (coded as '0') and a significant main effect or interaction in favour of iCT-R indicates intervention superiority (comparison of highest priority) of the newly developed resilience intervention over the existing online intervention. In a second step, iCT-R (coded as '1') is then tested against Standard Practice

(coded as '0') and again, a significant main effect or interaction in favour of iCT-R indicates intervention superiority for the newly developed intervention over usual Standard Practice. In a third step, Mind-Online (coded as '1') is tested against Standard Practice (coded as '0') and a significant main effect or interaction in favour of Mind-Online indicates intervention superiority of the existing online intervention compared to Standard Practice.

Adjusted/ estimated mean differences and Cohen's d's with standard deviation at baseline in the denominator are reported in tables for continuous outcomes for the intervention effects from results of linear mixed effects models and frequencies of diagnoses (absolute numbers and percentages) and absolute values as well as estimated/ adjusted odds ratios are reported for dichotomous outcomes.

All significance tests are carried out on a  $p < .05$  level, two-sided, and confidence intervals are reported on the 95% level.

Analyses of secondary trial objectives:

Any intervention effects on the secondary outcome measures, such as resilience (Connor-Davidson Resilience Scale,; Wagnild Resilience Scale), rumination (ruminative responses brooding subscale; Responses to Intrusions Questionnaire rumination subscale), anxiety (GAD-7), Smoking Behaviour (Smoking Behaviour Questionnaire), Alcohol consumption (Alcohol Use Questionnaire), psychological distress (GHQ), well-being (Warwick Edinburgh Mental Wellbeing Scale), sleep quality (Insomnia severity index), and weight, are analysed for the short-term primary outcome time point of 1-year and for the long-term primary outcome time point of 2-years follow-up, once completed.

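### The SAP declares iCT-R superior on a group main effect or a group-by-time interaction, after a three-arm global test, and never makes the iCT-R versus Mind-Online contrast at 1 or 2 years the test

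*Combined protocol and SAP*

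**What the plan says.** The SAP's Objectives section asks whether iCT-R is "more effective than the existing Mind-Online intervention at 1-year and at 2-years follow-up". The Statistical Analysis Outline states that "1-year follow-up is the short-term primary outcome time point", and Outcome Definitions adds: "Once the trial has been completed, the primary outcome time point is 2-years follow-up".

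The decision rule names no visit. Under Statistical Significance and Multiple Testing, "one or the other, main effects of intervention group or interaction effects between intervention group and time in favour of iCT-R, indicate intervention superiority". That sentence allows for exceptions, but none is given. Analysis Methods repeats the rule for the iCT-R versus Mind-Online pair: "a significant main effect or interaction in favour of iCT-R indicates intervention superiority (comparison of highest priority". Before that step, the Statistical Analysis Outline requires a three-arm test: "further group comparisons are carried out if the global comparisons are significant". No multiplicity adjustment is made.

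Time is categorical. For the symptom models (PCL-5, PHQ-9), Analysis Methods lists post-intervention, 6 months, 1 year and later 2 years. For the primary outcome, SCID-5 diagnoses, it lists no time levels. It does give that model a time-by-group interaction, and Timing of Final Analysis says that the 2-year data will be added to the 1-year models. Protocol section 11.1.1 plans a chi-square comparison of rates, also without a named visit.

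**The concern.** With two or more follow-up visits and an interaction in the model, the group main effect is either the effect averaged over visits or, under dummy coding, the effect at the reference visit. The interaction shows only that the effect differs between visits. With three visits the pairwise interaction has two degrees of freedom and no single direction, so a finding in favour of iCT-R is not defined for it.

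Three consequences follow:

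- A short-lived post-intervention effect could be reported as success on a 1- or 2-year objective.
- Accepting either term gives two chances of a false claim.
- The highest-priority comparison can be blocked by a global test that includes Standard Practice, although the sample size was set for one two-arm comparison.

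Because the coding, the link between global and pairwise tests, and the deciding term are all left open, they could be settled after the data are seen.

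**Working it through.** **The plan's own sample size.** Protocol 11.2 gives 25% versus 12.5%, two-sided 0.05 and 80% power. The mean rate is 0.1875.

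n = [1.96·√(2·0.1875·0.8125) + 0.8416·√(0.25·0.75 + 0.125·0.875)]² / 0.125² = (1.0819 + 0.4586)² / 0.015625 ≈ 151.9, so 152 per arm.

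Then 2 × 152 = 304, 3 × 152 = 456 and 456/0.80 = 570, as stated. The planned N therefore fits one two-arm comparison at one time point, with no global test and no either/or rule.

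**Assumptions for the illustration.** The documents give no within-person correlation, so 0.3–0.5 is assumed, with 2 or 3 follow-up visits and 152 per arm. A normal approximation stands in for the logistic mixed model. The effect at a single visit is 2.8 standard errors (1.96 + 0.84, that is, 80% power there). The interaction counts as favouring iCT-R if the change from first to last visit does.

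**Averaged main effect when only one of T visits carries the effect.** Before the global test:

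z = (2.8/T) / √[(1 + (T−1)ρ)/T]

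- T = 2, ρ = 0.3: 1.4/0.806 = 1.74, significant in 41%.
- T = 2, ρ = 0.5: 1.4/0.866 = 1.62, 37%.
- T = 3, ρ = 0.3: 0.933/0.730 = 1.28, 25%.
- T = 3, ρ = 0.5: 0.933/0.816 = 1.14, 21%.

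**Two chances.** Two independent tests at 5% give 1 − 0.95² = 9.75% two-sided, and 1 − 0.975² = 4.9% in favour of iCT-R.

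**Simulation with the global test included.** Standard Practice equals Mind-Online unless noted.

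| Truth | Rule as written declares iCT-R superior | Final-visit contrast |
|---|---|---|
| Effect at 6 weeks only, averaged main effect | 14–33% if the global main effect must be significant; 20–39% if either global test suffices | 2.5% |
| Same, main effect dummy coded at 6 weeks | about 76%; about 69% if Standard Practice lies midway | 2.5% |
| iCT-R = Mind-Online, both better than Standard Practice | about 5% | 2.5% |
| All three arms equal | about 2.5% | 2.5% |
| Effect at final visit only | 70–84% | 80% |
| Same, Standard Practice midway | 63–78% | 80% |
| Constant effect | 88–96% | 80% |

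In the third row, the two-sided error is 9–10% if either global test opens both pairwise tests. It is about 7% if each global test opens only its own and Standard Practice differs by a constant amount; about half of that, 7/2 = 3.5%, favours iCT-R. The SAP does not say which linkage applies.

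**Cost of the global test alone.** At one visit, with 152 per arm and 12.5% versus 25%, the pairwise chi-square has about 81% power. Requiring the three-arm test first gives 76% if Standard Practice is 25%, and 70% if it is 18.75–20%.

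**The case against.** The strongest reply concerns the primary outcome. Post-intervention is listed as a time level only for the symptom models, and the SAP treats symptom severity as secondary within the primary objective. If the diagnosis model held 1-year data alone, its group main effect would be the 1-year difference. If it held 1 and 2 years, the main effect would average the two visits named in the objective. Analysis Methods also frames its aim as differences at those visits and speaks of pairwise contrasts. This stands as an ambiguity. A reader might infer that the diagnosis model certainly includes the 6-week visit, and the text does not establish that. But its interaction needs at least two visits, diagnoses are collected post-intervention, and success is still defined by main effect or interaction.

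A reader might also infer that the rule generally misses late effects. It does not: with an effect at the final visit only it can exceed the direct contrast (up to 84% against 80%), and with a constant effect it does better still.

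Nor is the global test worthless. It is a recognised three-arm procedure and holds false superiority near 2.5% when all arms are equal. Its cost is moderate if Standard Practice performs like Mind-Online (76% against 81%). The 70% figure needs Standard Practice to do better than Mind-Online.

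Finally, the 9–10% error is two-sided. The rule requires a result in favour of iCT-R, so the like-for-like comparison is about 5% against 2.5%.

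**Conclusion.** The concern holds in this form: the SAP asks about iCT-R versus Mind-Online at 1 and 2 years, but decides on terms that, with several visits in the model, do not measure the difference at either visit. No section makes the visit-specific contrast the test.

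The serious consequence is a claim from an effect that has gone: about 14–39% of trials under averaged coding, or 69–76% if dummy coded at 6 weeks, against 2.5%. False superiority roughly doubles, to about 5%, when both programmes beat Standard Practice and either global test opens both pairwise tests. It does not double when all arms are equal. Power may fall or rise, so loss of power is not the main argument.

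That the rule departs from the stated question follows from the SAP text. The percentages rest on assumed correlations, deliberately extreme one-visit effects and a normal approximation. For the diagnosis model, the 6-week figures apply only if that visit is included, which the SAP leaves open.

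**What to change.** In Statistical Analysis Outline, Statistical Significance and Multiple Testing, and Analysis Methods, replace the either/or rule with wording such as:

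*The primary test is the model-based iCT-R versus Mind-Online contrast (adjusted odds ratio, 95% CI, two-sided 0.05) at 104 weeks, without a prior global test. iCT-R versus Standard Practice and then Mind-Online versus Standard Practice at the same visit follow in fixed sequence.*

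Also:

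- List the time levels of the diagnosis model.
- Use the same contrast at 52 weeks for the early analysis. State whether it is confirmatory and how alpha is shared with 104 weeks.
- Keep the time-averaged effect, the interaction and the global test as supportive results.

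Cost: the data and the model are unchanged. One contrast at 0.05 keeps 80% power with 152 per arm, so 570 stands. If both visits are confirmatory at 0.025 each, power at 152 per arm is about 71%; restoring 80% would need 185 per arm, 3 × 185 = 555, and 555/0.80 ≈ 694 in total. If the effect is constant over time, the change gives up the extra power of the time-averaged test (about 88–96% against 80%). Under the fixed sequence, a failed first comparison leaves the two comparisons with Standard Practice descriptive. How PTSD and MDD share the primary claim is a separate question that this wording does not settle.
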